# The impact of catheter replacement in patients with catheter-associated urinary tract infection: study protocol paper for a multicentre, non-inferiority randomized controlled trial (REPLACE)

**DOI:** 10.1186/s12879-026-12890-x

**Published:** 2026-02-27

**Keywords:** Urinary tract infection, Catheter associated urinary tract infection, Catheter, Catheter related infection, Urosepsis

## Abstract

**Background:**

Catheter-associated urinary tract infection (CAUTI) is the most common healthcare associated infection. Current guidelines state that catheters should be replaced in patients with CAUTI to hasten symptom resolution and to lower the risk of recurrence. However, the available literature is limited and there is significant practice variation globally. The aim of this study is to determine whether not changing the catheter during CAUTI treatment affects the recurrence-risk.

**Methods and analysis:**

The REPLACE study is a multicentre, non-inferiority- randomized controlled trial designed to assess whether retaining the urinary catheter in patients with CAUTI is non-inferior to replacement in terms of the risk of a recurrent CAUTI within 90 days. Secondary outcome measures include 30-day mortality, health-related quality of life, time to resolution of CAUTI symptoms, complications related to catheter replacement and healthcare and societal costs. Patients aged 18 years or older with an indwelling catheter (transurethral or suprapubic) and CAUTI are eligible. CAUTI is defined according to the Infectious Diseases Society of America (IDSA) criteria. Three hundred patient will be randomised 1:1 to catheter retention (intervention group) or replacement (control group). In the intervention group, the catheter is not replaced. In the control group the catheter will be replaced within 3 days after start of antibiotic therapy. The primary outcome (recurrent CAUTI within 90 days) will be assessed for non-inferiority (margin of 10%).

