#### Inclusion criteria

To be eligible to participate in this study, a subject must meet all of the following criteria:

Aged ≥ 18 years.Indwelling transurethral or suprapubic catheter for at least 2 weeks.CAUTI according to the IDSA guideline criteria, i.e.,
At least one of the following symptoms: onset or worsening of fever (> 38 degrees), rigors, altered mental status, malaise or lethargy with no other identified cause, flank pain, costovertebral angle tenderness, acute haematuria, pelvic discomfort, or suprapubic pain/tenderness. In patients with spinal cord injury: increased spasticity, autonomic dysreflexia, or sense of unease.Urine culture with ≥ 10^3^ colony-forming units (CFU)/mL of ≥ 1 bacterial species, or < 10^3^ CFU/mL along with a positive blood culture with the same microorganism as the urine culture.
The ability to provide written informed consent.

Participants may be enrolled before culture results are available. Consequently, participants may be excluded after inclusion (and randomization) if they are later found not to meet the microbiological criterion.

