### Statistical analysis

#### Sample size

It is planned to recruit 300 participants (150 in each treatment arm). For both groups, we assume a recurrence rate of 10% [18] within 90 days after start of antibiotic therapy. Analyzing the data as a non-inferiority study, taking a non-inferiority margin of 10%, and a (one-sided) type-I error rate (alpha) of 2.5%, a study with 300 participants would have a power of approximately 80%. A power of 80% would indicate that the likelihood is 80% that the upper-limit of the 95% confidence interval for the 90-day risk difference will exclude a difference of 10% in favour of the control (replacement) group. To account for post-randomization exclusions, we plan to randomize 400 participants.

An interim analysis of the overall recurrence rate will be performed after 50% of the initially planned sample size has completed 90 days of follow-up. The interim analysis will not assess treatment effectiveness, and no early stopping for efficacy or futility is planned. The sole purpose of this interim analysis is to evaluate whether the observed overall recurrence rate aligns with the assumptions used for the sample size calculation. If the recurrence rate is found to be below 7.5%, the project group will consider whether an increase in the sample size is warranted.

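### The abstract randomises 300 patients and the sample size section 400; the stated power of about 80% belongs to 300 patients left after exclusions, not to 300 randomised

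*Protocol article*

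**What the plan says.** Two places in the protocol article give the number of patients.

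- Abstract, Methods and analysis: "Three hundred patient will be randomised 1:1 to catheter retention (intervention group) or replacement (control group").
- Statistical analysis, Sample size, opening sentence: "It is planned to recruit 300 participants (150 in each treatment arm").
- Same section, on power: "a study with 300 participants would have a power of approximately 80" per cent. The inputs are that "we assume a recurrence rate of 10% [18] within 90 days after start of antibiotic therapy" in both groups, and "taking a non-inferiority margin of 10%, and a (one-sided) type-I error rate (alpha) of 2.5" per cent.
- Same section, after the power statement: "To account for post-randomization exclusions, we plan to randomize 400 participants".

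The reason for the larger number is in the Inclusion criteria section. Patients can be enrolled before the culture result is known, so that "participants may be excluded after inclusion (and randomization) if they are later found not to meet the microbiological criterion".

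The Sample size section also places a pooled check of the recurrence rate "after 50% of the initially planned sample size has completed 90 days of follow-up".

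**The concern.** The abstract and the Sample size section use the same verb for the same trial and give different numbers, 300 and 400. The opening sentence of the Sample size section adds to the conflict, because a trial cannot recruit 300 patients and randomise 400. The figures fit together only if 300 means the patients who remain after exclusions, and the article never says so.

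The difference matters because the power statement belongs to one of the two numbers only. If randomisation stopped at the abstract's 300, every later exclusion would come out of the 300 on which the power rests. The chance of missing non-inferiority when the arms are truly equal would then rise. The Implications section says that a failure to show non-inferiority would be taken to strengthen the case for replacement, so a failure due only to a small sample could be misread.

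**Working it through.** **Inputs, all from the Sample size section unless noted**

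- Recurrence risk p = 0.10 in both arms, so the true difference is 0.
- Margin 0.10 on the risk difference; one-sided alpha 0.025 (z = 1.96).
- Success: the upper limit of the two-sided 95% interval lies below 0.10.
- 1:1 allocation (Randomization section).
- 300 participants for the power statement, 400 to be randomised.

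**Step 1. Reproduce the stated power.** With n analysed per arm and the unpooled normal approximation,

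power = Φ(0.10 / √(2p(1 − p)/n) − 1.96), where 2p(1 − p) = 2 × 0.10 × 0.90 = 0.18.

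For n = 150: √(0.18/150) = 0.0346; 0.10/0.0346 = 2.887; 2.887 − 1.96 = 0.927; Φ = 0.823.

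Exact binomial enumeration at 150 per arm gives 81.9% with the Wald interval, 80.3% with the Newcombe interval and 80.3% with the Farrington-Manning score rule. A continuity-corrected Wald rule gives 77%. The stated figure of about 80% is reproduced for 300 analysed patients. The normal approximation needs 142 per arm (284 in total) for 80%, so 300 has a small reserve.

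**Step 2. The exclusion allowance.** Going from 400 randomised to 300 remaining implies (400 − 300)/400 = 25%. The article does not state this rate.

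**Step 3. Power if only 300 are randomised.** Exclusions are assumed equal in the two arms, and excluded patients are assumed to leave the primary analysis. Same formula:

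| Excluded | Analysed per arm | Power |
|---|---|---|
| 0% | 150 | 82.3% |
| 5% | 142.5 | 80.3% |
| 10% | 135 | 78.2% |
| 15% | 127.5 | 75.9% |
| 20% | 120 | 73.3% |
| 25% | 112.5 | 70.5% |
| 30% | 105 | 67.6% |

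The 25% row in full: 300 × 0.75 = 225, or 112.5 per arm; √(0.18/112.5) = 0.040; 0.10/0.040 = 2.50; 2.50 − 1.96 = 0.54; Φ = 0.705. Exact enumeration at 112 and 113 per arm gives 71% to 72% (Wald), 68% (Newcombe) and 67% to 68% (Farrington-Manning).

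By the normal approximation, power falls below 80% once exclusions pass (300 − 284)/300 = 5.3%.

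**Step 4. Power under the methods text.** 400 × 0.75 = 300, which returns to the first row and the stated power.

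**The case against.** The strongest reply is that the Sample size section can be followed as it stands: power is calculated for 300, and the number randomised is raised to 400 because some patients will be excluded. On that reading the defect is one wrong figure in an abstract and one loose verb, and the trial as planned keeps its power. Most of this stands. It does not remove the contradiction, because the abstract gives a definite and different number for the same quantity.

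A reader might infer more than the article supports in four ways.

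- **That the 80% is miscalculated.** It is not; Step 1 reproduces it for 300 analysed patients.
- **That the trial will have 70% power.** This needs two conditions: stopping at 300 randomised, which the methods do not plan, and losing 25%, a rate that is only implied. The 400 could be a rounded or cautious ceiling.
- **That missing outcomes reduce the number further.** The article gives no rate of missing outcomes. The Analyses of outcome measures section plans multiple imputation in the primary analysis, so these patients are not simply removed from it.
- **That the interim trigger is a separate error.** Half of the initially planned sample size most naturally refers to the 300 named at the start of the same section, hence 150 patients. The check uses the overall recurrence rate, does not assess treatment effectiveness and has no stopping rule for efficacy or futility. Nothing shows that 150 or 200 would alter the trial's conclusion.

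**Conclusion.** The point holds as an inconsistency in a core design number. The abstract's 300 randomised conflicts with the 400 in the Sample size section, and the sentence about recruiting 300 adds to the conflict. The power of about 80% is right for 300 analysable patients (80% to 82%, or 77% under a continuity-corrected rule). It would not hold for 300 randomised once exclusions exceed about 5%: about 78% at 10% excluded, 73% at 20%, and just over 70% at the implied 25%. In the last case the risk of missing non-inferiority, when the arms are equal, rises from about 18% to about 30% by the normal approximation.

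These figures rest on the plan's own 10% recurrence in both arms, equal exclusion across arms, and excluded patients leaving the primary analysis. The contradiction itself rests on no assumption. It should be corrected, but it does not call the design into question.

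**What to change.** Correct the abstract and the opening sentence of the Sample size section so that both say 400 patients will be randomised to obtain 300 analysable (150 per arm). State the assumed rate of post-randomisation exclusion next to the 400; if it is 25%, say so. If the intention is in fact to randomise only 300, restate the power for the number expected to remain after exclusions.

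The same edit can make the interim trigger explicit, for example by giving the number of patients meant (most naturally 150) and saying whether excluded patients count. This is a clarification only.

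The cost is a few words in two places. The design and analysis do not change, and no patients are needed beyond the 400 already planned.

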**Discussion:**

This trial will address a critical evidence gap and may inform future guidelines regarding catheter management in CAUTI. If replacement is found to have no benefit, this could reduce unnecessary interventions, lower healthcare costs and material use, contribute to sustainability, and lessen the burden on both patients and healthcare organizations.

**Trial registration:**

Registered at clinicaltrial.gov on 17 April 2025 with registration number: NCT06936631.

**Supplementary Information:**

The online version contains supplementary material available at 10.1186/s12879-026-12890-x.

## Background

Due to the widespread use of urinary catheters, catheter-associated urinary tract infection (CAUTI) is the most common healthcare-associated infection [1]. As urinary catheter use is expected to rise with an aging population, the number of CAUTIs will likely increase accordingly [2]. CAUTIs can result in serious, sometimes fatal complications, including urosepsis [3–6].

To fasten recovery and reduce the risk of recurrent CAUTI, current guidelines recommend to replace the catheter at the onset of CAUTI when the indwelling catheter has been in place for more than two weeks [1, 6, 7]. This recommendation, however, is based on limited evidence as only four conflicting studies have been identified that investigate catheter replacement during CAUTI [8]. Current guidelines rely on only one of these four studies which is a small randomized controlled trial (RCT) that favoured catheter replacement [9]. The study reported shorter recovery times and lower recurrence rates in the replacement group compared to the retention group. These findings were contradicted by a second RCT [10], which found higher recurrence rates in the replacement group. However, in that study, antimicrobial treatment was shorter in the replacement group. Two observational studies found no effect of catheter replacement on either recurrence or symptom duration [11, 12], highlighting the paucity of the current state of evidence on catheter management during CAUTI.

In light of the limited evidence, a survey has been conducted to assess clinical practice regarding catheter management in CAUTI (manuscript in preparation [13]). It revealed considerable variation in catheter management practices among urologists, microbiologists, and internists. Urologists indicated more often that they routinely retain the transurethral catheter, compared to internists and medical microbiologists. The primary reasons for catheter replacement were the fact that it is a guideline recommendation and the expectation that replacement would be beneficial from a pathophysiological rationale. From a theoretical perspective, catheter replacement aligns with the principle of source control, as removal of the catheter may eliminate biofilm-associated pathogens that can persist during antimicrobial therapy and contribute to recurrent CAUTI [14]. Main reasons for retaining the catheter were the lack of scientific evidence supporting clinical benefit and the risk of procedural complications of the procedure.

The REPLACE study aims to generate evidence to inform future recommendations for urinary catheter management in the treatment of CAUTI. We hypothesize that not changing the catheter during a CAUTI is non-inferior to replacing it with regard to the risk of recurrent CAUTI. This study therefore potentially contributes to reducing healthcare costs and sustainability by minimizing waste generated from catheter replacements, while also alleviating the workload on personnel when the procedure is redundant.

## Methods

### Study design and setting

This study is a multicentre, two-arm, randomized controlled non-inferiority trial. Patients will be recruited from two academic and fifteen non-academic hospitals across the Netherlands between April 2025 and February 2028. The number of participating centres may be increased depending on the recruitment rate.

### Participants

Recruitment will occur in both inpatient and outpatient settings.

#### Inclusion criteria

To be eligible to participate in this study, a subject must meet all of the following criteria:

Aged ≥ 18 years.Indwelling transurethral or suprapubic catheter for at least 2 weeks.CAUTI according to the IDSA guideline criteria, i.e.,
At least one of the following symptoms: onset or worsening of fever (> 38 degrees), rigors, altered mental status, malaise or lethargy with no other identified cause, flank pain, costovertebral angle tenderness, acute haematuria, pelvic discomfort, or suprapubic pain/tenderness. In patients with spinal cord injury: increased spasticity, autonomic dysreflexia, or sense of unease.Urine culture with ≥ 10^3^ colony-forming units (CFU)/mL of ≥ 1 bacterial species, or < 10^3^ CFU/mL along with a positive blood culture with the same microorganism as the urine culture.
The ability to provide written informed consent.

Participants may be enrolled before culture results are available. Consequently, participants may be excluded after inclusion (and randomization) if they are later found not to meet the microbiological criterion.

#### Exclusion criteria

A potential participant who meets any of the following criteria will be excluded from participation in this study:

Antibiotic treatment initiated more than 3 days prior to inclusion.Immunodeficiency: High-dose corticosteroid use (any equivalent of ≥ 20 mg prednisolone per day for > 4 weeks), severe primary immunodeficiency, organ transplant, neutropenia (absolute neutrophil count < 0.50 × 10⁹/L).Discontinuation of the indication for the indwelling catheter.A planned (routine) catheter replacement during antibiotic therapy.Contraindications for catheter replacement.Kidney catheters (nephrostomy or double-J catheter).Needing continuous bladder irrigations because of gross haematuria.Bladder stones.Pregnancy.A life expectancy of less than 90 days, as estimated by the treating physician.

### Study interventions

Patients will be assessed for CAUTI according to standard practice of care. Potential participants will be screened against inclusion/exclusion criteria by the central study team. Eligible patients will receive written study information and provide written or remote informed consent before randomization.

After obtaining informed consent, participants will be randomized to either catheter replacement (control group) or catheter retention (intervention group). In the replacement group, the catheter will be replaced within 3 days of starting antibiotic treatment. All patients (men and women) will receive a 10-day course of antibiotics. The choice of antibiotic agent is at the discretion of the treating physician, except for nitrofurantoin, fosfomycin, and trimethoprim as these may be considered inferior for the treatment of CAUTI with systemic symptoms. Once culture and susceptibility results are available, therapy must be adjusted according to the EUCAST susceptibility criteria.

### Randomization

Patients will be allocated to the control or intervention group using the Castor Electronic Data Capture (EDC) system, in a 1:1 ratio. Stratified randomization will not be applied, as no single dominant prognostic factor for recurrence is known.

### Data collection

Patients will be followed for a total period of 180 days, with seven telephone visits (Table 1). All follow-ups are done by a member of the central study team at the LUMC. Data will be collected on patient characteristics, symptoms, and urine analyses, and several questionnaires will be administered.

#### Clinical data

At baseline, the following patient characteristics will be recorded: gender, age, height, weight, vital signs, social circumstances, medical history, medication use, catheter specific data (type of catheter, duration). The length of hospital stay, intensive care unit (ICU) admission during hospitalization, and type and treatment duration of antimicrobial agent(s) will additionally be collected.

Upon inclusion, CAUTI symptoms will be recorded, including onset or worsening of fever (> 38 degrees), rigors, altered mental status, malaise or lethargy with no other identified cause, flank pain, costovertebral angle tenderness, acute haematuria, pelvic discomfort, or suprapubic pain/tenderness. In patients with spinal cord injury increased spasticity, autonomic dysreflexia, or sense of unease will be assessed. Participants will be provided with a paper diary to record their symptoms for the first 14 days after start of antibiotic treatment. During each follow-up visit, CAUTI symptoms will be reassessed to track symptom duration and identify possible CAUTI recurrences.

#### Laboratory data

Urine samples will be collected according to standard of care for microbiological culture. Uropathogens growing at ≥ 10³ CFU/mL will be identified and subjected to susceptibility testing according to standard laboratory protocols. If obtained as part of routine clinical care, blood culture results, inflammation parameters, kidney function and lactate will be collected from the medical records.

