### Outcome measures

The primary outcome is a recurrent CAUTI within 90 days after completion of antibiotic treatment, defined according to the same IDSA-based clinical and microbiological criteria used for inclusion. The pathogen does not have to be identical to the causative pathogen that was identified during the first episode.

All participants are instructed to contact the central study team should they experience CAUTI symptoms. Additionally, the physicians at the participating centres and general practitioners are instructed to report potential recurrences among participants.

Secondary outcomes:

Patient-related outcomes: 30-day mortality, health-related quality of life assessed using the PROMIS and EQ-5D-5L questionnaires.Process-related outcomes: time to resolution of CAUTI symptoms, time to resolution of fever, complications of catheter replacement and severity of the complications (5-level Likert scale).Resource-related outcomes: length of hospital stay, ICU-admission during hospital stay, healthcare and societal cost using a selection of items relevant for this population of the medical consumption (iMCQ) and productivity (iPCQ) questionnaire.

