#### Analyses of outcome measures

Descriptive statistics will be used to summarize baseline characteristics. In the primary analysis, the risk difference with (two-sided) 95% confidence interval will be computed to compare the differences in 90-day recurrence risk between the two treatment arms, in both the intention-to-treat population and the per-protocol population. Regarding the primary analysis, multiple imputation will be used to deal with missing outcome data (i.e. missing information regarding CAUTI recurrence). For the primary outcome, three sensitivity analyses will be performed to account for missing data. In the first sensitivity analysis, a complete case analysis will be performed. Additionally, a worst-case and best-case scenario analysis will be performed, in which patients who drop out of the study before 90 days will be included under the assumption that they experienced a recurrence (worst-case scenario) or no recurrence (best-case scenario), respectively.

The primary analysis will not take patient characteristics into account, as these are expected to be balanced between treatment groups (by randomization). In a secondary analysis, multivariable analysis will be performed including variables that are associated with recurrence of CAUTI.

The secondary outcome time-to-resolution will be analysed using Kaplan Meier survival analysis. For patient-related outcomes measures, such as PROMIS and EQ-5D-5 L, repeated measures analyses will be performed to compare these outcomes between the groups. For these outcome measures, multiple imputation will be used to deal with missing outcome data. Process and resource related outcome measures will be analysed in the per-protocol population. In addition, a cost-effectiveness analysis from a societal perspective with a 6-month time horizon and a budget impact analysis will be performed.

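### The primary endpoint needs a urine culture, but none is secured at a suspected recurrence and the handling of uncultured episodes is unstated; counting them as non-events at similar rates in both arms would favour non-inferiority

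*Protocol article*

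**What the plan says.** All references are to the protocol article.

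- **Outcome measures.** The primary outcome is recurrent CAUTI within 90 days, "defined according to the same IDSA-based clinical and microbiological criteria used for inclusion".
- **Inclusion criteria.** The microbiological criterion is at least 10^3 CFU/mL of one or more bacterial species in urine, or a lower count "CFU/mL along with a positive blood culture with the same microorganism as the urine culture". Both routes need a urine culture.
- **Laboratory data.** "Urine samples will be collected according to standard of care for microbiological culture". The sentence does not separate baseline from follow-up samples.
- **Data collection and Clinical data.** Follow-up is by seven telephone visits. "During each follow-up visit, CAUTI symptoms will be reassessed to track symptom duration and identify possible CAUTI recurrences".
- **Outcome measures, on finding recurrences.** "All participants are instructed to contact the central study team should they experience CAUTI symptoms". Site physicians and "general practitioners are instructed to report potential recurrences among participants". Neither instruction mentions a culture.
- **Analyses of outcome measures.** Missing information on recurrence is multiply imputed. A complete-case analysis is planned, as are worst-case and best-case analyses; the worst case is one "in which patients who drop out of the study before 90 days will be included under the assumption that they experienced a recurrence".

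**The concern.** A recurrence can be real, symptomatic and treated, yet fail the endpoint definition because no urine was cultured. Follow-up is by telephone and care is given by general practitioners and site physicians, so nothing in the stated procedures guarantees a sample.

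A patient treated in this way who stays in the study has not dropped out, so the worst-case and best-case analyses do not apply. Multiple imputation would apply only if the episode is classed as missing, and the article does not say that it is.

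What is at stake is the type I error of the non-inferiority test. Missing the same share of events in both arms multiplies the absolute risk difference by the detected share, while the margin stays at 10 points. A retention strategy that is truly at the margin then looks better than it is. The trial is open, so the decision to culture may also depend on the arm.

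**Working it through.** **Inputs from Sample size:** 150 per arm, 10% recurrence assumed in both arms, margin 10 percentage points, one-sided alpha 2.5% (upper limit of the two-sided 95% interval below 10 points), power about 80%.

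**Assumed input:** the share of true recurrences that are cultured and so detected, s_R (retention) and s_C (replacement). The article gives no value; equal shares of 70% to 100% and several unequal pairs are shown.

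**Step 1, the plan's own figure.** With 10% in both arms, SE = √(2 × 0.10 × 0.90 / 150) = 0.0346. Power = Φ(0.10/0.0346 − 1.96) = 82.3%. Exact binomial enumeration gives 81.9% with the Wald interval and 80.3% with the Newcombe interval. The stated 80% or so is reproduced.

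**Step 2, model.** Suppose an uncultured recurrence is scored as a non-event and there are no false positives. The observed risks are then s_R × p_R and s_C × p_C. Take retention truly at the margin: p_R = 0.20, p_C = 0.10. The false non-inferiority rate is the probability that (observed difference + 1.96 × SE) is below 0.10, by enumerating two binomials with n = 150.

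**Step 3, equal detection.** The observed difference is s × 0.10.

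| Detected, both arms | Observed risks | Observed difference | False non-inferiority |
|---|---|---|---|
| 100% | 20% v 10% | 10 points | 2.7% |
| 95% | 19% v 9.5% | 9.5 points | 3.6% |
| 90% | 18% v 9% | 9 points | 4.7% |
| 80% | 16% v 8% | 8 points | 8.2% |
| 70% | 14% v 7% | 7 points | 14.2% |

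The choice of interval matters little: Newcombe limits give 2.5%, 4.3%, 7.5% and 12.8% at 100%, 90%, 80% and 70%.

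**Step 4, unequal detection.** The observed difference is 0.20 × s_R − 0.10 × s_C.

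| Retention | Replacement | Observed difference | False non-inferiority |
|---|---|---|---|
| 80% | 90% | 16 − 9 = 7 points | 12.6% |
| 80% | 70% | 16 − 7 = 9 points | 5.0% |
| 90% | 80% | 18 − 8 = 10 points | 2.7% |
| 90% | 70% | 18 − 7 = 11 points | 1.5% |

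The observed difference stays at 10 points when 0.20 × s_R − 0.10 × s_C = 0.10, that is, when (1 − s_C) = 2 × (1 − s_R). In this scenario the bias cancels when the replacement arm misses twice the share missed under retention, and reverses beyond that.

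**Step 5, would the plan notice?** Under equal true risks of 10%, 80% detection gives observed risks of 8% and nominal power of 89.1% (Wald approximation), so power appears to improve. The interim check has a trigger of 7.5% on the pooled rate, and 0.75 × 10% = 7.5%. It cannot distinguish a low true rate from missed cultures.

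**The case against.** The strongest reply is that the article does not say what a reader might infer from it. Three inferences go too far.

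- **That cultures are taken only in routine care.** The Laboratory data sentence contains no such restriction and may simply describe how samples are handled. The same section makes blood cultures and other tests conditional on having been obtained in routine care, and does not put urine in that list. The full protocol, not shown, may require a culture at a suspected recurrence.
- **That uncultured episodes are scored as no recurrence.** No section states this. The imputation rule covers missing information on recurrence in general and is not tied to dropout, so it could cover these episodes.
- **That the trial is necessarily pulled towards non-inferiority.** Closer culturing of patients who keep their catheter is plausible in an open trial, and Step 4 shows that it can cancel or reverse the effect.

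The article also describes active case-finding and acknowledges reporting bias and misclassification. The detection shares are assumed, and at 95% detection in both arms the effect is small (3.6%).

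These points make the concern conditional but do not remove it. As written, an episode without a urine culture cannot meet the definition, the recurrence instructions cover reporting only, and no sensitivity analysis reaches a patient who is treated and remains in follow-up. The listed mitigations (symptom definitions, structured questionnaires, central follow-up) do not produce a culture. Two reasonable analysts could classify the same episode differently, and that choice affects the type I error.

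**Conclusion.** The concern holds in conditional form. The endpoint depends on a culture that the stated procedures do not secure, and the classification of treated, uncultured episodes is open. If they are counted as non-events at similar rates in both arms, the error rate at the margin rises from 2.7% to between 4.7% and 14.2% for assumed detection of 90% down to 70%. With unequal culturing, the rate in the cases shown runs from 1.5% (90% retention v 70% replacement) to 12.6% (80% v 90%).

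These sizes rest on true risks of 20% v 10%, 150 analysed per arm, no false-positive events and assumed detection shares. The article does not establish that bias will occur, nor its direction. It does leave the result exposed to a choice that should be settled before outcome data are seen.

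**What to change.** 1. **Outcome measures.** Add to the existing instruction to participants, site physicians and general practitioners a request that a urine culture be obtained at every suspected recurrence. Record for each episode whether one was taken, and report this by arm.
2. **Analyses of outcome measures.** State that a suspected recurrence that was treated but has no usable culture is missing and is imputed, not scored as no recurrence.
3. **Sensitivity analysis.** Add one that counts these episodes as recurrences, reported by arm.

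**Cost.** One line in an existing instruction, one case-report field, one coding rule and one extra analysis. Expect a few more routine cultures and slightly wider intervals from imputation. The sensitivity analysis will admit some false positives, because symptoms such as malaise or lethargy are non-specific. False positives at similar rates in both arms also dilute an absolute difference, so this analysis should be supportive only. If the full protocol already requires a culture at suspected recurrence, item 1 reduces to a clarifying clause.
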